| **Concept and Rationale:**  Up to 95% of anal cancers (anal squamous cell cancers, ASCC) are caused by human papillomavirus (HPV)[1](#_ENREF_1); however, current management of pre-cancerous lesions (anal intraepithelial neoplasia, AIN) consists of surgical excision or ablation and this does not treat the underlying cause of HPV infection. Recurrences are common; in HIV-seronegative persons treated with ablation, recurrence is as high as 50% within one year [2](#_ENREF_2). The morbidity of these destructive ablations is significant and includes anal stenosis and fecal incontinence.  Artesunate, formulated as a suppository, is WHO-approved for first-line treatment for acute malaria in children who are located in remote settings with limited access to healthcare [3](#_ENREF_3). Globally, Artesunate has been administered to 2 million people [4](#_ENREF_4), given orally, intramuscularly, intravenously, and as rectal suppositories, providing a wealth of safety information. Both Artesunate and dihydroartemisinin, an Artesunate metabolite, have been shown to be cytotoxic to epithelial cells expressing HPV16 E6 and/or E7, while having no effect on uninfected cells [5](#_ENREF_5). Both ASCC and AIN2/3 (high-grade anal intraepithelial neoplasia) are associated with functionally obligate expression of two viral proteins, E6 and E7. Epithelial cells that express either or both of these oncoproteins overexpress the transferrin receptor, and have increased levels of intracellular iron, compared to normal cells [6](#_ENREF_6). Artesunate contains an endoperoxide bridge that reacts with intracellular ferrous iron to generate free radicals, leading to cell death .  This observation raises the possibility of treating pre-invasive HPV disease (i.e., AIN2/3) with an effective anti-malarial drug, Artesunate, administered as an intra-anal suppository. The toxicity profile of this formulation is well-documented and includes dizziness, nausea, emesis, and abdominal pain. It should be noted that these symptoms are also commonly experienced in active malarial infection. Preliminary data from an ongoing study of intravaginal administration of Artesunate suppositories for cervical dysplasia has demonstrated mucosal irritation as the only adverse event.  This study investigates a novel non-surgical approach to the treatment of HPV-associated anal intraepithelial neoplasia, using topical Artesunate. |
| **Primary Objective(s):**  To evaluate the safety and tolerability of intra-anal administration of Artesunate, administered via suppository with 3 different schedules, in patients with high-grade anal intraepithelial neoplasia (AIN 2/3). |
| **Secondary Objective(s):**   - - 1. To measure the effect of intra-anal topical Artesunate administration determined by pathology, based on the regression of AIN2/3 at study weeks 16, 28, and 40. Regression defined as either AIN1 or no AIN lesion detected by HRA/biopsy and anal cytology.     2. To evaluate clearance of HPV as assessed by Hybrid Capture 2 DNA testing of cytologic specimens.     3. Collection patient specimens into tissue bank for future studies. |
| **Primary Endpoint(s):** Maximum safe dose of Artesunate. |
| **Secondary Endpoint(s):**   - - - - Tissue concentrations of Artesunate       - Change in pathology from AIN2/3 to AIN 1 or no evidence of AIN through the measurement of HPV genotyping.       - Tissue bank of specimens for future studies |
| **Study Design:**  This is a Phase I modified 3 + 3 design, in which the maximum tolerated dose (MTD) will be identified. The 3 + 3 dose escalation will consist of 6 dose levels in combination with variation in dosing schedules of the single-agent Artesunate. This design also allows for some possible intermediate doses to be examined if dose limiting toxicities (DLTs) occur and de-escalation is needed. An expansion cohort will occur at the MTD. Once the MTD is determined, then secondary outcomes will be evaluated. |
| **Number of Patients:** At Johns Hopkins Hospital, 6 new patients with the diagnosis of high-grade intraepithelial lesion (HSIL) are seen per month in our institution’s High-Resolution Anoscopy Clinic, which is our anal cancer screening clinic. Each year, over 72 new patients with the diagnosis of AIN 2/3 are seen. There is currently a 6-month waitlist for the High-Resolution Anoscopy Clinic. We anticipate that we will enroll 40% of our patients due to compliance and follow-up patterns studied in our HRA Clinic.  At the University of Wisconsin, on average 9 new patients with the diagnosis of high-grade anal intraepithelial neoplasia (HGAIN) are seen per month in our institution’s High-Resolution Anoscopy Clinic, which is our anal cancer screening clinic.  We anticipate the study duration to be 2 years. |
| **Main Criteria for Inclusion/Exclusion:**  Inclusion criteria:   - Age ≥ 18 years - Biopsy-confirmed high-grade anal dysplasia (AIN 2, AIN 3, HSIL) by HRA. This includes patients who are newly diagnosed with AIN 2/3 as well as those who have recurrent AIN 2/3 after medical therapy or surgical therapy. - Adequate contraceptive use for males and females of reproductive potential. - Female of childbearing potential: negative urine pregnancy test - Able to provide informed consent - Patients who have the ability to collaborate with planned follow-up (transportation, compliance history, etc.) - Patients who have and have not been immunized with the HPV vaccine. - Weight ≥50 kg.   Exclusion criteria:   - Age < 18 years - Diagnosis of low-grade anal dysplasia (AIN 1, LSIL) by HRA - Known anal, vulvar, cervical, or penile cancer - CD4 count < 200 at the time of consideration for entry into this study. Patients, whose CD4 counts drop below 200 at any timepoint in this study will be treated with the standard of care treatment arm of surgical ablation. - Unable to provide informed consent - Currently receiving systemic chemotherapy or radiation therapy for another cancer. - Patients who are on medical treatment with systemic immunosuppressants or steroids (e.g., active autoimmune disease) - Extensive anal condyloma precludes the ability for the clinician to visualize HSIL during HRA - Pregnant female - Weight < 50 kg. |
| **Intervention and Mode of Delivery:**  Artesunate suppositories will be administered transanally. Doses of escalation will be 200 mg, 400 mg, and 600 mg. Suppositories will be administered daily for 5 days. Five days constitutes 1 cycle. Up to 3 cycles will be administered at Weeks 0, 2, and 4. |
| **Duration of Intervention and Evaluation:**  Patients will undergo initial screening by HRA to evaluate candidates who have AIN 2/3. Week 0 starts when the patient starts their first cycle of Artesunate. Patients may take up to 3 cycles of Artesunate on Weeks 0, 2, and 4. HRA and biopsy will be performed at 3 month-intervals (Week 16, 28, 40), which is the standard of care for interval follow-up for AIN 2/3. |
| **Statistical Methods**:   1. **Definition of primary outcome/endpoint:** This is a Phase I modified 3 + 3 design, in which the MTD will be identified. 2. **Definition of secondary outcomes/endpoints:**  - Downgrade in AIN 2/3 to AIN 1 or no AIN - HPV genotype testing—optimally to undetectable levels of HPV at week 40 of follow. - Creating of tissue bank for future studies.   **Analytic plan for primary objective:** This is a Phase I modified 3 + 3 design, in which the MTD will be identified. Based on previous studies of rectally administered Artesunate for the treatment of malaria, the safety profile demonstrates a low probability of dose limiting toxicity in children, as well as adults. The initial dose will be a 200 mg suppository administered in cycles of 5 daily doses at weeks 0 and 2. Dose escalation will proceed with a 3 + 3 design with the safeguard of an integrated de-escalation schema. At the MTD, an expansion cohort of 12 patients will be included.  Note: Each cycle = 5 days   | **Dose Escalation Design** | | | | | | --- | --- | --- | --- | --- | | **Cohort** | **Dose (mg)** | **Number of Treatment Cycles** | **Designated Weeks of Artesunate Administration** | **Number of patients** | | **I** | 200 | 2 | 0, 2 | 3 | | **II** | 200 | 3 | 0, 2, 4 | 3 | | **III** | 400 | 2 | 0, 2 | 3 | | **IV** | 400 | 3 | 0, 2, 4 | 3 | | **V** | 600 | 2 | 0, 2 | 3 | | **VI** | 600 | 3 | 0, 2, 4 | 3 |   ***According to the standard of care clinical practice, a postoperative visit will be done 4 weeks after ablation, i.e. either on week 20 or on week 32   1. **Analytic plan for secondary objectives:**     1. For the dichotomous variables of regression of AIN 2/3, counts, percents and 95% confidence levels will be calculated.    2. HPV viral genotyping will be assessed to determine when HPV viral load will become undetectable.    3. Tissue bank of specimens for future studies. 2. **Sample size justification:** In this phase I dose escalation trial, 6 dose levels will be considered for a total sample size of 36-60 patients with a target dose limiting toxicity (DLT) of < 18%. |
| **Funding, Regulatory, and Feasibility Issues:**  Frantz Viral Therapeutics will supply the Artesunate suppositories at no cost. The suppository will be obtained from an off-site pharmacy (Buderer Drug Company).  Buderer Drug Company will ship suppositories to the Johns Hopkins Hospital Investigational Drug Pharmacy for each patient enrolled in the study. |
| **Patient Acceptability/Ethics and Consent Issues:** The issue that may limit patient or advocate acceptance would be compliance to follow-up, as patients will be on a strict schedule of up to 3 cycles of Artesunate suppository administration. Education of administration of the suppositories will be performed at the beginning of each cycle by the research nurse coordinator and a follow-up phone call at the end of each cycle of administration will determine any adverse events. Standard of care consists of surgical ablation and patients may opt to proceed with surgery at any time during this study. |

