The primary strategy to decrease disease burden in HPV-infected individuals is to intervene when premalignant anal disease, AIN2/3, is detected prior to the development of ASCC. All treatments for AIN2/3 are ablative and include electrocauterization/fulguration, hyfrecation, laser vaporization. Because they involve tissue destruction, all current therapeutic options have the potential for adverse sequelae, such as pain, fecal incontinence, and anal stenosis. Furthermore, these ablative techniques are not curative. Recurrences are common; in HIV-seronegative persons treated with ablation, recurrence is as high as 50% within one year of ablation.[2](#_ENREF_2) In HIV-positive individuals, recurrence rates are as high as 68%.[10](#_ENREF_10) An effective topical intervention that targets the underlying cause, HPV, would obviate the need for surgery and prevent progression to ASCC.

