## Exclusion Criteria

- Age < 18 years
- Diagnosis of low-grade anal dysplasia (AIN 1, LSIL) by HRA
- Known anal, vulvar, cervical, or penile cancer
- CD4 count < 200 at the time of consideration for entry into this study. Patients, whose CD4 counts drop below 200 at any timepoint in this study, will be pulled to the standard of care treatment arm of surgical ablation.
- Unable to provide informed consent
- Currently receiving systemic chemotherapy or radiation therapy for another cancer.
- Patients who are on medical treatment with systemic immunosuppressants or steroids (e.g., active autoimmune disease)
- Extensive anal condyloma precludes the ability for the clinician to visualize HSIL during HRA
- Pregnant female
- Weight < 50 kg.

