## Data Reporting

The frequency and severity of all toxicities will be tabulated from CRFs and summarized for review in a descriptive fashion. All CRFs will be reviewed by the principal investigator on a weekly basis with the research team. The initial review of toxicity will be completed after the first treatment group has completed the intervention portion of the study.

Data collected at study visits at both institutions will be entered into the study REDCap database housed at Johns Hopkins.

The secondary efficacy endpoints will be compared with analogous data obtained in an open prospective database, “Development of a Prospective HRA Database” (Johns Hopkins IRB# [NA_00078993](https://e-irb.jhmi.edu/eirb2/Rooms/DisplayPages/LayoutInitial?Container=com.webridge.entity.Entity%5BOID%5B1E381BBFC925834D936BB3B006F85B94%5D%5D) ). This observational cohort protocol has been open since 2012 and includes over 250 subjects. These subjects are all of the patients that have been treated with HRA and ablation in the Johns Hopkins HRA Clinic. We will compare changes in HPV viral load and AIN pathology from baseline to HRA evaluation at 16, 28, and 40 weeks.

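### Section 10.1 sets a selected trial population against an unrestricted clinic database, so the efficacy comparison is confounded in a direction and by an amount the protocol does not fix

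*Protocol*

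**What the plan says.** Protocol section 10.1 (Data Reporting) commits to an external comparison: "The secondary efficacy endpoints will be compared with analogous data obtained in an open prospective database". The database "has been open since 2012 and includes over 250 subjects", and its membership is defined: "These subjects are all of the patients that have been treated with HRA and ablation in the Johns Hopkins HRA Clinic". Changes in HPV viral load and AIN pathology from baseline to the HRA at weeks 16, 28 and 40 are to be compared. No restriction, matching or adjustment is stated. Section 14.3 and the synopsis analytic plan give only proportions with 95% intervals and do not mention the database.

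The trial population is defined in sections 3.1 and 3.2. Entry needs biopsy-confirmed AIN2/3, ability to keep to planned follow-up (compliance history is named) and life expectancy above 2 years. Among the exclusions are "CD4 count < 200 at the time of consideration for entry into this study" and "Patients who are on medical treatment with systemic immunosuppressants or steroids", along with known anogenital cancer and current chemotherapy or radiotherapy. Recurrent AIN2/3 after earlier medical or surgical therapy is eligible. Section 11.1 replaces anyone who does not come back for at least the week 16 visit. The synopsis names the University of Wisconsin as a second source of patients and says of Johns Hopkins: "We anticipate that we will enroll 40% of our patients due to compliance and follow-up patterns studied in our HRA Clinic".

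**The concern.** The comparator is everyone the clinic ablated; the trial group is a filtered part of such a population, plus patients from another centre. The two would be expected to differ in immune status, attendance and disease history even if they had received the same treatment. Any difference in AIN or HPV outcome then mixes the effect of artesunate with the effect of who was let in.

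What is at stake is how the efficacy signal from a small phase I trial is read. A contrast with more than 250 patients can look weightier than it is, and a larger comparator does not remove this kind of bias. The dose-finding conclusion is not involved.

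**Working it through.** **1. What the 40% is.** The synopsis gives 6 new patients per month at Johns Hopkins and 9 at Wisconsin. Section 14.2 expects 6 evaluable patients per month.

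- 0.40 × (6 + 9) = 6.0 per month. This reproduces the stated accrual if the 40%, which is given for Johns Hopkins only, is assumed for Wisconsin too.
- Johns Hopkins alone: 0.40 × 6 = 2.4 per month.
- 6 × 12 = 72 per year, which agrees with the synopsis's figure of over 72.

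So the 40% is an accrual forecast, attributed to compliance and follow-up. It supports the view that attendance will select patients. It says nothing about CD4 count or immunosuppression.

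**2. The two populations side by side.**

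| Feature | Trial | Database (section 10.1) |
| --- | --- | --- |
| Site | Johns Hopkins and Wisconsin | Johns Hopkins only |
| Lesion | AIN2/3, biopsy-confirmed (3.1) | Treated with HRA and ablation; grade not stated |
| CD4 below 200 | Excluded (3.2) | No exclusion stated |
| Systemic immunosuppressants or steroids | Excluded (3.2) | No exclusion stated |
| Ability to comply | Required (3.1) | No requirement stated |
| Not back by week 16 | Replaced (11.1) | No rule stated |
| New or recurrent disease | Both eligible (3.1) | Mix not stated |

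**3. Direction and size.** The documents do not give the database's mix of HIV status, CD4 count, immunosuppression, attendance or prior treatment, so no corrected figure can be computed. The following are illustrations under stated assumptions. Each is taken alone; a positive sign favours artesunate.

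- *Compliance.* Assume the database mirrors a clinic in which 40% would be selected and 60% would not. The difference is p(selected) − [0.40 × p(selected) + 0.60 × p(others)] = 0.60 × gap. Assumed gaps of 10, 20 and 30 points give +6, +12 and +18 points.
- *Recurrent disease.* Assume it is 30 to 50 points more common in the trial and lowers success by 10 to 30 points. The difference is −(excess share × penalty), which runs from −0.30 × 10 = −3 to −0.50 × 30 = −15 points.
- *HIV mix.* The difference is the HIV effect × (HIV-positive share in the database − share in the trial). Neither share is given, so the sign is open. HIV-positive patients who meet the CD4 limit remain eligible (section 8.3.4).

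Single sources of selection therefore span about −15 to +18 points under these assumptions.

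**4. Precision, for scale.** Section 14.1 provides for 12 patients in total at the MTD, where section 14.3 evaluates the secondary outcomes. Exact 95% intervals are 21% to 79% for 6/12 and 5% to 57% for 3/12.

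**The case against.** **This is detail for a statistical analysis plan.** Matching and adjustment methods commonly are, and a plan may exist. But the protocol itself names the comparator population as everyone treated. That is a stated choice, and following it as written gives non-comparable groups.

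**The comparison carries little weight.** It is secondary, no test, margin or decision rule uses it, and with 12 patients the sampling error is as large as any plausible bias. This stands. It limits how serious the point is, and it is why a descriptive label suffices. It also means that splitting the section 14.3 regression proportion by HIV status would add little: with strata near 6, an observed 3/6 has an interval of about 12% to 88%.

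**Poor attenders drop out of the comparator anyway.** A change measured at weeks 16, 28 and 40 needs an HRA at those times, so database patients without one contribute nothing. This partly stands: the compliance figures above probably overstate that component. It does not touch immune status, site or disease history.

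**Matching would not isolate the drug.** Database patients were ablated, and under section 8.3.8 trial patients with residual disease are ablated from week 16. This is correct and is a separate limitation. Restriction removes one source of non-comparability, not all.

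**Stronger readings a reader might infer.** One is that the comparison is biased in artesunate's favour. That is plausible for the immune and compliance exclusions, but recurrent disease is admitted and could work the other way, and the database mix is unknown.

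Another is a point estimate from section 2.1, which gives recurrence up to 50% in HIV-negative patients and states "In HIV-positive individuals, recurrence rates are as high as 68" per cent. The gap is 68 − 50 = 18 points, and scaling it by HIV-share differences of 10 to 50 points gives 1.8 to 9 points. That is not a measure of bias here. Both figures are upper values; they describe recurrence rather than regression after a suppository; only the 50% has a stated time frame (one year); and they split by HIV status rather than by CD4 count.

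**Conclusion.** The point holds for section 10.1. As written, the trial is compared with a population it was not drawn from under the same rules, and nothing stated corrects for this. The conclusion rests on the protocol's own definitions of the two groups and needs no assumption about the database's content beyond its description.

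Neither sign nor size can be derived from the documents. The −15 to +18 points show only that plausible selection effects can run either way and be of moderate size. A claim that artesunate is favoured, or a numerical bias built on the recurrence figures, would go beyond the text. The 40% forecast is supporting evidence on attendance at Johns Hopkins and is not itself an error.

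The change is worth making because it is specific and cheap. It is not critical: the MTD does not depend on it.

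**What to change.** In section 10.1, if the comparison is kept:

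- Restrict the comparator to database patients who would have met sections 3.1 and 3.2 at their baseline HRA, as far as the database records those items, and who have assessments in the week 16, 28 and 40 windows (each ± 2 weeks in the visit table of section 8.2). List the criteria that cannot be checked.
- Describe both groups by HIV status and by new versus recurrent AIN2/3, and standardise the database to the trial's mix where numbers allow.
- Label the comparison descriptive.

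If the database lacks the main fields, the comparison could be dropped.

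The cost is wording and a filter on an existing database. On the trial side the data are already collected: HIV status (8.3.2), previous therapies (8.3.3) and CD4 count if HIV-positive (8.3.4). Sections 3.2 and 8.3.4 treat a CD4 count of exactly 200 differently and should be reconciled before the filter is written. The downside is a comparator smaller than the stated 250, possibly too small to standardise. No change to section 14.3 is needed for this point.

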**Schema**

[figure not shown]

[figure not shown]

[figure not shown]

[figure not shown]

**Screening visit—HRA, anal pap, HPV genotyping**

**Week 0 (Cycle 1)**

Artesunate suppositories

A

**Week 2 (Cycle 2)**

Artesunate suppositories (Anoscopy)

**Week 4 (Cycle 3)**

Artesunate suppositories (Anoscopy )

**Week 16**

Assess for residual disease: HRA + biopsy + pap smear + HPV genotyping

Some improvement observed:

- Lesion size by office HRA
- AIN grade reduction (Biopsy, pap smear)

No improvement

Ablation in OR

**Week 28**

Assess for residual disease: HRA + biopsy + pap smear + HPV genotyping

No detection of AIN2/3 lesion by biopsy + anal pap smear

Detection of AIN2/3 lesion by biopsy + anal pap smear

Ablation in OR***

**Week 40**

Assess for relapsing disease: pap smear and if clinically indicated HRA + biopsy + HPV genotyping

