## Secondary Objectives

- - 1. To measure the effect of intra-anal topical Artesunate administration determined by pathology, based on the regression of AIN2/3 at study weeks 16, 28, and 40. Regression defined as either AIN1 or no AIN lesion detected by HRA/biopsy and anal cytology.
    2. To evaluate the clearance of HPV as assessed by HPV genotype testing of cytologic specimens.

1.2.3 To create a tissue bank for future studies.

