## Duration of Follow Up

Patients will be followed for a total of 40 weeks from the first day of administration of the study drug or until death, whichever occurs first. Patients removed from study treatment for unacceptable adverse event(s) will be followed until resolution or stabilization of the adverse event.

Please see the schematic diagram for treatment follow-up as outlined in the Protocol Synopsis section.

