# BIOMARKER, CORRELATIVE, AND SPECIAL STUDIES

- Downgrade in AIN 2/3 to AIN 1 or no AIN by HRA evaluation
- Decrease in HPV genotype testing by PCR of anal pap test sample—optimally to undetectable levels of HPV at week 40 of follow-up.
- Creation of tissue bank of specimens obtained from patients.

Please note that the highlighted tests above are depicted in the flow diagram and timeline in the schematic diagram on the next page.

##
[figure not shown]

[figure not shown]

[figure not shown]

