**Week 40**

Assess for relapsing disease: pap smear and if clinically indicated HRA + biopsy + HPV genotyping

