# 8.3.7 HIGH-RESOLUTION ANOSCOPY examination

Patients will undergo serial HRA examinations; at the screening visit, and at weeks 16, 28, and 40. Exfoliated cell samples will be obtained using at the time of HRA, for anal cytology, HPV typing, and for tissue bank storage. Anoscopy will be performed and the anal canal will be visualized with a Zeiss colposcope. Serial applications of 5% acetic acid followed by Lugol’s solution into the anal canal will be analyzed by an anoscope to identify vascular abnormalities. Biopsies will be obtained with an endoscopic cold forceps biopsy. Specimens will be stored in formalin. Specimens for HPV genotyping will be processed by the Atila Biosystems. Specimens for the tissue bank will be directed to the biorepository owned by [name], where they will be processed and cryopreserved for analysis in future studies.

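### The protocol contradicts itself on whether week 40 HPV genotyping is done for every patient or only when clinically indicated

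*Protocol*

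**What the plan says.** The week 40 box of the synopsis schema, repeated in the section 7 schema, gives the purpose of the visit as a check for relapse and lists: "pap smear and if clinically indicated HRA + biopsy + HPV genotyping". The week 28 box carries no condition: "Assess for residual disease: HRA + biopsy + pap smear + HPV genotyping". Week 16 lists the same procedures as week 28.

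HPV clearance is a secondary objective (section 1.2): "To evaluate the clearance of HPV as assessed by HPV genotype testing of cytologic specimens". That objective names no week. The Statistical Methods part of the synopsis does, with the wording "optimally to undetectable levels of HPV at week 40 of follow", and section 7 repeats it as "optimally to undetectable levels of HPV at week 40 of follow-up".

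Other parts of the protocol treat week 40 as a routine assessment:

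- Appendix A marks HPV testing, HRA, anal pap and anal brushes at week 40, with no footnote or condition in that column.
- Section 8.3.7 lists week 40 among the HRA examinations that patients undergo. At each HRA, exfoliated cells are taken "for anal cytology, HPV typing, and for tissue bank storage".
- The synopsis (Duration of Intervention and Evaluation) schedules HRA and biopsy at weeks 16, 28 and 40.
- Section 10.1 plans to compare HPV and pathology changes from baseline at 16, 28 and 40 weeks.

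**The concern.** At the one week that the protocol attaches to undetectable HPV, two diagrams make the HPV test depend on clinical judgement, while the calendar makes it routine. The stated purpose of the schema's week 40 visit is to look for relapse, so the indication for testing would be suspected relapse. That suspicion is plausibly related to persistent HPV. Results would then be missing for reasons tied to the outcome itself, mostly in patients who look well.

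Two institutions enrol, and each could follow a different part of the protocol in good faith. A week 40 genotype that was never obtained may not be recoverable at analysis. What is at stake is a secondary endpoint, not the primary safety question.

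**Working it through.** **Step 1. Compare the places that bear on week 40.**

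| Place in protocol | HPV test at week 40 | HRA at week 40 |
| --- | --- | --- |
| Synopsis schema | Conditional | Conditional |
| Section 7 schema | Conditional | Conditional |
| Appendix A | All patients | All patients |
| Section 8.3.7 | Sample taken at each HRA | Scheduled, no condition |
| Synopsis, Duration of Intervention and Evaluation | Not mentioned | Scheduled with biopsy, no condition |
| Section 10.1 | Compared at week 40 | Compared at week 40 |

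**Step 2. Look for a rule of precedence.** There is none. Section 5.4 says: "Please see the schematic diagram for treatment follow-up as outlined in the Protocol Synopsis section". Section 7, just after stating the week 40 HPV outcome, also refers to the diagram. Section 8 refers instead to the study calendar in Appendix A.

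**Step 3. Direction of the effect if the schema is followed.** The protocol gives no figure to reproduce, so this is an illustration and all three inputs are assumptions. Let c be the true proportion HPV-clear at week 40, t1 the probability of being tested if clear, and t0 the probability of being tested if not clear.

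Observed clearance among tested = c·t1 / (c·t1 + (1 − c)·t0)

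With c = 0.30, t1 = 0.30 and t0 = 0.80: 0.09 / (0.09 + 0.56) = 0.09 / 0.65 = 13.8%, with 65% of patients tested.

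| Assumed true clearance | t1/t0 = 0.5/0.8 | t1/t0 = 0.3/0.8 | t1/t0 = 0.2/0.9 |
| --- | --- | --- | --- |
| 20% | 13.5% | 8.6% | 5.3% |
| 30% | 21.1% | 13.8% | 8.7% |
| 50% | 38.5% | 27.3% | 18.2% |

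**Step 4. If the calendar is followed.** Then t1 = t0 = 1 and the formula returns c. Bias from selective testing is zero.

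**Step 5. What selective testing could do in the MTD cohort.** Section 14.1 allows a total of 12 patients at the MTD. Suppose 6 are tested and 2 of them are clear. The proportion over all 12 could then lie anywhere from 2/12 = 17% (no untested patient clear) to (2 + 6)/12 = 8/12 = 67% (all untested patients clear).

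**The case against.** The strongest reply is that the protocol read as a whole makes week 40 testing routine. Appendix A, section 8.3.7, the synopsis text and section 10.1 all point that way, against one diagram printed twice. Section 8.3.7 ties the HPV sample to HRA, but it also schedules week 40 HRA without a condition, so it sides with the calendar. This stands. A reader might infer that the plan measures week 40 clearance mainly in patients with suspected relapse and is therefore biased by design. The documents do not support that: the bias arises only where a site acts on the schema.

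Week 40 is also not the only HPV measurement. Genotyping is unconditional at weeks 16 and 28, and the calendar and synopsis schema add week 6. Section 14.3 describes genotype longitudinally and qualitatively, and the week 40 target is worded as an optimum. This also stands and limits the consequence. It does not remove it, because earlier results cannot stand in for the week 40 result, and selective gaps at the last visit affect a longitudinal description too.

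The illustration uses assumed rates. It also leaves out ablation after week 16 or week 28, which already complicates reading week 40 HPV status as a drug effect. Both criticisms are fair, so the figures show direction only. Finally, the schema was read as detached text boxes, so its arrows are not visible. The sentence could be parsed differently, but its natural reading makes genotyping conditional.

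**Conclusion.** The point holds as an internal contradiction. Both schemas make week 40 HPV genotyping conditional, other parts of the protocol make it routine, and the cross-references point both ways. Where a site follows the schema, week 40 clearance among tested patients would likely be biased low, assuming that suspicion of relapse is related to HPV persistence. Where every site follows the calendar, there is no such bias. The documents give neither a clearance rate nor a testing rate, so the size cannot be stated; the tabulated range of 5.3% to 38.5% against assumed true values of 20% to 50% is illustrative.

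The same clause puts week 40 HRA and biopsy in conflict with the rest of the protocol. HRA conflicts with Appendix A, section 8.3.7 and the synopsis text, and biopsy with the synopsis text. This bears on regression at week 40, which section 1.2 names as an assessment time. The matter should be corrected, but it concerns secondary endpoints of a phase I safety trial.

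**What to change.** In both schemas, move HPV genotyping out of the conditional clause, so that week 40 lists pap smear and HPV genotyping for all patients, in agreement with Appendix A. The assay can use the pap or brush sample already scheduled for everyone at that visit.

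State that patients without a week 40 HPV result are reported as missing and not counted as cleared. No passage proposes counting them as cleared; the sentence simply closes the gap, and it may sit in the SAP if it is not already there.

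Separately, reconcile the schemas with Appendix A, section 8.3.7 and the synopsis text on whether week 40 HRA and biopsy apply to every patient. That is a clinical decision for the sponsor and investigators; the need here is for one consistent statement.

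The cost is a wording change and at most one assay per patient, so no more than 60 at the maximum accrual in section 14.2. The calendar already lists these assays, and no extra visit or sample is needed.
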